#### Primary outcome measures

2.4.1

We will use the international scar evaluation method: “*Vancouver Scar Evaluation Scale*” as the main standard for evaluating the efficacy.

(1)Color: 3 points for bright red, 2 points for light red, and disappear after pressing, 1 point for non-red or some gray, 0 points for normal skin color;(2)Height of scar marks: 3 points above 9 mm, 5 mm < 2 points for height ≤9 mm, 1 point for 1–5 mm, 0 points for flat or slightly depressed;(3)Hardness: 3 points for hard as cartilage, 2 points for hardness like rubber, 1 point for softness, normal for softness Skin score: 0 points;(4)Itching: 3 points for severe or persistent itching, 2 points for frequent and tolerable itching, sometimes 1 point for itching, and 0 points for no itching;(5)Pain: very intense 3 points for the “hyperalgesia”, 2 points for moderate-intensity allergic pain, sometimes 1 point for pain, and 0 points for no pain;(6)tightness: 3 points for strong tightness, not too tight Strong and tolerable score 2 points, slight tightness score, no tightness score 0 points. Efficacy index = (total score before treatment-total score after treatment) / total score before treatment × 100%.

#### Efficacy evaluation

2.4.2

Refer to “*Guidelines for Clinical Research of New Chinese Medicine*”. Efficacy was evaluated by the ratio of the difference between the points before and after treatment compared to the points before treatment. Syndrome treatment efficiency = (total points before treatment total points after treatment) / total points before treatment × 100%.

(1)Clinical control: clinical symptoms and signs disappeared or basically disappeared, and syndrome scores were reduced by ≥95%;(2)Significant effect: clinical symptoms and signs were significantly improved, and syndrome scores were reduced by 70%; The signs and symptoms have improved, and the syndrome scores have decreased by ≥30%;(3)Ineffective: the clinical symptoms and signs have not improved significantly, and the syndrome scores have decreased by less than 30%.

### Sample size calculation

2.5

The sample size for this trial is based on an expected mean difference between groups of 11 points of the Constant–Murley questionnaire, which is the minimum clinically important difference. To detect this difference between both treatments, with a value of a = 0.05 (probability of committing a type I error) and a statistical power of 95%, a minimum of 49 patients per group is needed. This minimal sample size estimate has been increased by 20% after considering the potential dropouts, finally including 60 patients for each group. Accordingly, the proposed experimental hypothesis is that there will be a difference of at least 11 points in the Constant—Murley questionnaire in the intervention group versus the control group. The sample size was determined using the Stata SE software.

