#### Diagnostic criteria

2.2.1

We will refer to the diagnostic criteria for pathological scars in “*Plastic Surgery*”. We will refer to the “Beauty Surgery” published by the People's Medical Publishing House (Beijing, China). The specific standards are as follows:

(1)HS occurs in various parts of the human body and occurs 4 weeks after trauma.(2)The lesion is limited to the scope of the wound; the early color is bright red and hard; it often shows excessive keratinization, ulceration and contracture; the texture and bulge of the mature stage are beyond the original damage range, and the mature stage is from June to December.(3)Consciously itching and burning pain in different degrees.(4)Symptoms can disappear after several months to 1 to 2 years, and gradually become dark brown, tending to be stable.

In addition, we will refer to the *“Vancouver Scar Scale”* combined with accompanying symptoms to develop scoring criteria, and then grade the severity of HS. The scale has a total score of 21 points. A higher score indicates more severe scarring. Mild: Total points ≤7. Moderate: 7 <total points ≤15. Severe: Total points> 15.

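### The sample size, the 95% power and the experimental hypothesis rest on an 11-point Constant–Murley difference, an instrument this trial does not measure

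*Protocol article*

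**What the plan says.** All references are to the protocol article.

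- **Sizing endpoint and effect (2.5, Sample size calculation).** "The sample size for this trial is based on an expected mean difference between groups of 11 points of the Constant–Murley questionnaire". The section presents those 11 points as the smallest difference that matters clinically.
- **Error rates and n (2.5).** Alpha is 0.05 with sidedness not stated. The section gives "a statistical power of 95%, a minimum of 49 patients per group is needed". No SD is given.
- **Allowance for loss (2.5).** "This minimal sample size estimate has been increased by 20% after considering the potential dropouts, finally including 60 patients for each group". This agrees with the 120 patients in the abstract.
- **Hypothesis (2.5).** "the proposed experimental hypothesis is that there will be a difference of at least 11 points in the Constant—Murley questionnaire", intervention against control.
- **Primary outcome (2.4.1, Primary outcome measures).** A version of the Vancouver scar scale serves "as the main standard for evaluating the efficacy". It has six items (colour, height, hardness, itching, pain, tightness), each scored 0 to 3. The same section defines an efficacy index, the percentage fall from baseline, and 2.4.2 grades response on a percentage of the same form.
- **Range of the scale (2.2.1, Diagnostic criteria).** "The scale has a total score of 21 points". The six listed items sum to 18.
- **Design (2.3, Interventions).** Participants are self-controlled, with untreated scars of the same participants as the blank control.

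**The concern.** The Constant–Murley questionnaire appears only in section 2.5. It is absent from the assessments listed in the abstract, the outcome measures, the efficacy evaluation and the statistical analysis. Section 2.5 names it twice, the second time as the trial's hypothesis, so it cannot be passed over as a single slip of a word.

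If the instrument is not measured, no data the trial collects can test the stated hypothesis. The 95% power and the 49 evaluable patients per group then have no link to the endpoint that will be analysed. A null result could not be read as evidence against the planned difference. A positive one could not be judged against a stated important difference, because none is given in scar points.

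**Working it through.** **1. Inputs.** From 2.5: difference 11, alpha 0.05, power 95%, n = 49 per group. From 2.4.1: six items of 0 to 3, so a total of 0–18. From 2.2.1: a total of 21. The documents give no SD and no sidedness, so both sidedness readings are tried.

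**2. Reproducing 49 per group.** For two independent means, n = 2(z₁₋α/₂ + z₁₋β)² × SD² / difference².

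- Two-sided: (1.960 + 1.645)² = 12.99. With SD 15, n = 2 × 12.99 × 225 / 121 = 48.3, so 49. Any SD from 14.95 to 15.10 rounds up to 49. The noncentral t gives a standardised difference of 0.736 and SD = 11 / 0.736 = 14.95.
- One-sided: the SD would be 16.4 to 16.6.

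The calculation is therefore coherent for some instrument with an SD near 15. The arithmetic is not the fault.

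**3. Can those inputs belong to the raw scar total?** The SD of a score bounded between 0 and M is at most M / 2.

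| Range of total | Largest possible SD | 11 points as share of range | n per group for 11 points at that SD |
|---|---|---|---|
| 0–18 | 9 | 61% | 18 |
| 0–21 | 10.5 | 52% | 24 |

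Even with the largest SD possible, 11 points would need only 18 or 24 per group. So 49 cannot be obtained from an 11-point difference in a raw scar total, on either stated range.

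**4. What power does the trial have on its own scale?** This needs an SD and a difference that the documents do not give. The values below are assumptions (raw scar total, two independent groups, two-sided 0.05, normal approximation).

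| Difference | SD | n per group for 95% power | Power with 49 per group |
|---|---|---|---|
| 1 | 2 | 104 | 70% |
| 1 | 3 | 234 | 38% |
| 2 | 3 | 59 | 91% |
| 2 | 4 | 104 | 70% |
| 3 | 4 | 47 | 96% |
| 3 | 5 | 73 | 84% |

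The power lies on either side of 95%, depending on values nobody has stated.

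**5. What N = 120 delivers.** Assume 20% of patients are lost.

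- Two groups: 60 × 0.8 = 48 per group. The difference detectable with 95% power is 0.743 SD (noncentral t). For assumed SDs of 2, 3, 4 and 5 points that is 1.5, 2.2, 3.0 and 3.7 points.
- Self-controlled: 120 × 0.8 = 96 pairs, assuming one treated–untreated pair per patient. The detectable difference is 0.372 SD of the within-patient difference.

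The second SD is a different quantity from the first, so the two results cannot be compared without knowing the correlation between a patient's own scar areas. The design therefore decides which formula applies.

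**The case against.** The strongest reply is that the bound on the SD covers only one choice of analysis variable. That is correct. The bound of 9 or 10.5 is for a raw total at one time. A change score on 0–18 can run from −18 to +18, so its SD can reach 18. The percentage efficacy index in 2.4.1 is on another scale, where 11 points with SD 15 is not excluded. The bound therefore shows that the inputs were not derived for the raw total, and no more. It does not rescue section 2.5, which names neither a change score nor the percentage index as the variable it sizes on.

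Three stronger readings may tempt a reader, and the document does not support them.

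- **That an 11-point effect is impossible because many scars start at 10 or less.** That limits the improvement of one scar. Section 2.5 plans a difference between groups, and untreated scars may worsen.
- **That the allowance for loss is wrong.** Section 2.5 says the estimate was raised by 20%. 49 × 1.2 = 58.8, and 60 fits those words. Sixty per group tolerates a loss of 18.3%. If exactly 20% were lost, 48 would remain against 49, and power for the planned standardised difference would be 94.6% in place of 95%. Nothing turns on this.
- **That the trial is underpowered.** See the verdict.

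Condensation for a journal, or an analysis plan that is not shown, does not answer the point. The missing SD alone might be excused on those grounds. Here the article positively states a sizing endpoint, an effect and a hypothesis that do not belong to the trial it describes.

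**Conclusion.** The point holds. Section 2.5 sizes the trial and states its hypothesis on an instrument outside the trial's outcomes, and this is plain from the document without any assumption. The implied SD of about 15 (two-sided) confirms that the figures were not worked out for the raw scar total, whichever of the two stated ranges is used. The 95% power is therefore not a property of this trial. The calculation also uses independent groups where section 2.3 describes self-control.

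A reader might infer that the true power is too low. That is not shown: over the assumed differences of 1 to 3 points and SDs of 2 to 5 points tabulated above, power with 49 per group runs from 38% to 96%. The correct statement is that it is unknown. Nor does the mismatch by itself raise the type I error of whatever test is finally applied.

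**What to change.** 1. Delete the Constant–Murley difference and the hypothesis built on it.
2. Name the primary scar variable for sizing: raw total, change from baseline or percentage index, at a stated time point. Reconcile the 18-point and 21-point totals first.
3. Restate the hypothesis on that variable.
4. Give the assumed SD with its source, the difference of interest, the sidedness, and a formula that matches the design: two independent groups, or paired with the SD of within-patient differences.
5. Keep N = 120 and report the power or detectable difference it gives after the expected loss. At 20% loss and 95% power this is about 0.74 SD with 48 per group, or about 0.37 SD of the paired difference with 96 pairs.

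The cost is a rewritten section 2.5. Reporting what the fixed N delivers needs no change in recruitment, and the Ethics section (2.9) says that recruitment has not started. The downside is that the stated power may become less favourable than 95% once it is tied to a realistic difference on the scar score.

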### Randomization and blinding

2.6

(1)The concealment of random schemes: After the scheme design is completed, the random schemes are enclosed in a sequence-encoded, sealed, light-tight envelope. Then it is handed over to the person in charge of the subject, after screening qualified cases, the envelope is opened to determine the grouping.(2)The recorder fills in the case report form with basic data and observation of the patient's local and systemic symptoms.(3)Unified production of various documents.(4)Check and confirm the correctness and completeness of all research data records and reports and case report forms, and ensure consistency with original data.

### Statistical analysis

2.7

Data management uses EXCEL software to build a database, double entry, check for outstanding values, and lock. Statistical analysis will be performed using SPSS 25.0 software for statistical analysis. The normality of the measurement data is tested. The data obeying the normal distribution is Student's *t* test, which is expressed by mean ± standard deviation. The data not obeying the normal distribution is rank sum test. And marginal homogeneity test; count data are expressed by rate and composition ratio, and comparison is performed by chi-square test; repeated measurement data are expressed by mean ± standard deviation, intra-group comparison is performed by analysis of variance of repeated measurement data, and inter-group comparison is by multivariate analysis of variance (MANOVA). *P* ≤ .05 indicates that the difference is statistically significant.

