**Methods/design::**

In this study, we will use our own front-to-back clinical research method. We plan to include 120 young and middle-aged female patients who meet the diagnostic criteria for HS. The untreated HS of the enrolled patients will be used as blank controls. The intervention group will be given acupuncture treatment. The assessment of scar area, color, hardness, thickness, itching and pain will be recorded for 30 days of treatment.

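### The protocol lets the same scar result be judged as a total score, a percentage index or response grades, and across visits by MANOVA, each at P ≤ .05, without saying which decides efficacy

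*Protocol article*

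**What the plan says.** Section 2.4.1 (Primary outcome measures) makes the Vancouver scale the main standard for efficacy. It scores six items from 0 to 3 and then defines a percentage: "Efficacy index = (total score before treatment-total score after treatment) / total score before treatment × 100" per cent.

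Section 2.4.2 is headed Efficacy evaluation and is not marked as secondary. It uses the same quantity again, "Efficacy was evaluated by the ratio of the difference between the points before and after treatment compared to the points before treatment", and turns it into response grades with cut-offs at 30%, 70% and 95%.

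The abstract lists features rather than a total: "The assessment of scar area, color, hardness, thickness, itching and pain will be recorded for 30 days of treatment".

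Section 2.7 (Statistical analysis) chooses tests by type of data. Measurements get a t test, or a rank sum test if they are not normal. A marginal homogeneity test is named without saying for what. For the rest: "count data are expressed by rate and composition ratio, and comparison is performed by chi-square test; repeated measurement data are expressed by mean ± standard deviation". Between-group comparison of the repeated data is by MANOVA. One rule covers every test: P "≤ .05 indicates that the difference is statistically significant". No order, split of alpha or exploratory label is given.

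Section 2.5 (Sample size calculation) works "with a value of a = 0.05 (probability of committing a type I error) and a statistical power of 95" per cent, but for an "expected mean difference between groups of 11 points of the Constant–Murley questionnaire".

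**The concern.** A scale is not yet an endpoint. From this scale the protocol derives at least three results at any one visit: the total, the percentage fall and the grade. A fourth, the MANOVA, runs across visits. The four can disagree. The index divides by baseline, so a low starting score carries extra weight. The grades discard information within each band. The MANOVA asks whether the groups differ in any way over the visits, which is not the same as being better at the end of treatment.

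Two sections both claim to define efficacy, and one threshold applies to everything. A report could therefore rest the efficacy claim on whichever form is significant. In that case the 5% type I error in section 2.5 does not describe the claim. The sample size section usually shows which endpoint decides, but here it is built on an instrument that is not among the outcomes in section 2.4.

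**Working it through.** **The plan's own figure.** The protocol states no overall error rate across forms. Its only related figure is 49 per group, from n = 2(z₁₋α/₂ + z₁₋β)² SD² / Δ² with Δ = 11, α = 0.05 and power 95%. No SD is given, so 49 cannot be reproduced. Solving 49 = 2 × (1.960 + 1.645)² × SD² / 121 gives an SD of about 15.1 two-sided, or about 16.6 one-sided. A 20% allowance gives 49 × 1.2 ≈ 59 or 49 / 0.8 ≈ 62, close to the stated 60. None of this concerns the scar scale, so section 2.5 does not identify the deciding endpoint.

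**Reference values.** With k independent tests at 0.05, the chance of at least one false positive is 1 − 0.95^k: 9.8% for k = 2, 14.3% for k = 3 and 18.5% for k = 4. The forms are correlated, so the true values should be lower.

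**Simulation under no effect.**
- From the documents: 60 per group, six items scored 0 to 3, baseline and four visits (days 15, 30, 45 and 60), P ≤ .05.
- Assumed, because the documents do not give them: item correlation 0.2 to 0.7, visit correlation 0.3 to 0.8, the same improvement over time in both groups, two-sided tests, and grade cuts read as 30/70/95%.
- At one visit: t test on the total, rank sum (or t) test on the index, chi-square on the grade. Across visits: MANOVA on the four visit totals.

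| Situation | Chance of at least one P ≤ .05 |
|---|---|
| Independent groups, total + index + grade at one visit | about 8% to 12% |
| The same, plus MANOVA over four visits | about 11% to 16% |
| Independent groups, four forms, results favouring acupuncture only | about 6% to 9% (one test: 2.5%) |
| Self-controlled scars, paired tests, four forms | about 13% to 17% |
| Self-controlled scars (correlation 0.5), independent-sample tests | about 3% to 4% |
| One prespecified valid test | 5% |

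With a t test on the index and narrower correlations (items 0.2 to 0.5, visits 0.5 to 0.7; 4,000 replicates), the first two rows are 0.105 to 0.112 and 0.134 to 0.144. Taken singly, the total, the index and the MANOVA each reject at 0.040 to 0.054 and the chi-square at 0.031 to 0.036. The excess therefore comes from having several routes, not from a faulty test.

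In the directional and paired rows the MANOVA was run on the six items at the visit. Replacing it by the MANOVA over visits gave results of similar size. The wider ranges rest on 1,500 runs per setting, with standard error √(0.12 × 0.88 / 1500) ≈ 0.008, so their ends are uncertain by one to two percentage points.

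**The case against.** The strongest reply is that the protocol never says any one significant result is enough. It names a main scale under a primary heading and puts the grades under a separate one. Section 2.7 only matches tests to data types, with t and rank sum as alternatives rather than two attempts. This is also a condensed article, and ordering of secondary analyses is commonly left to a statistical analysis plan.

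Much of this stands. The forms are possible routes to a claim, not declared co-primary tests, so the percentages hold only if any form may count. They also depend on the design, which the protocol leaves contradictory. Section 2.3 describes self-controlled scars, while sections 2.5 and 2.6 describe groups of 60 allocated by envelope.

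Three stronger readings are tempting and not supported:
- A reader might count the MANOVA as a fourth test at a single visit. Section 2.7 assigns it to repeated measurement data, so once the visit is fixed only three forms remain.
- A reader might add the six items as separate tests, which would raise the simulated chance to 0.28 to 0.33. No section plans item-level tests: the abstract says only that features are recorded, and section 2.4.1 scores the items within the scale.
- A reader might take the two-sided figure as the chance of wrongly declaring acupuncture effective. It includes results against acupuncture, which is why the directional row is shown.

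The reply does not remove the core. Which result decides the trial is a protocol decision, and this article prints its outcome, sample size and analysis sections. Those sections give two unranked definitions of efficacy and one blanket threshold. The low 3% to 4% is no safeguard, since it arises only when the wrong kind of test is applied to paired data.

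**Conclusion.** The point holds in conditional form. The protocol does not say whether the total, the index or the grade decides efficacy, or how the MANOVA over visits relates to them, and it reads each at P ≤ .05. If any of them may carry the claim and the groups are independent, the two-sided error is about 1.6 to 2.4 times the nominal 5% for three forms at one visit (8/5 to 12/5). With the MANOVA over visits it is about 2.2 to 3.2 times (11/5 to 16/5). For results favouring acupuncture the ratio is similar (6/2.5 to 9/2.5, or 2.4 to 3.6).

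The documents do not support a single unconditional error rate. The correlations are assumed, sidedness is not stated, and the design is unresolved: the error is higher for paired tests and below 5% if independent-sample tests are misapplied. The correction should be made, but the gap does not by itself invalidate the trial.

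**What to change.** In sections 2.4.1 and 2.7, name one primary analysis: the acupuncture-versus-untreated difference in the scar total score at one named visit, two-sided 0.05. Day 30, the end of the stated course, is one candidate. Sections 2.3, 2.5 and 2.6 must first be reconciled so that the test matches the design: paired if scars are self-controlled, independent-sample if there are separate groups. State the range of the total as well, because the six items in 2.4.1 sum to at most 6 × 3 = 18 while section 2.2.1 gives 21.

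Label the efficacy index, the 2.4.2 grades, the MANOVA over visits and any single-item results as secondary. Either report them with estimates and confidence intervals and no efficacy claim, or test them in a fixed order only after the primary analysis succeeds.

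The cost is a few sentences. Section 2.9 says recruitment has not started, and no extra patients or data are needed. The small downside is that a favourable response grade alone can no longer be presented as proof of efficacy.

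### The efficacy grades are ordered, but the only test the plan ties to count data is chi-square, which ignores their order and, if patients are their own controls, their pairing

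*Protocol article*

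**What the plan says.** Section 2.4.2 (Efficacy evaluation) grades the percentage fall in total points from before to after treatment. The top grade is defined by "clinical symptoms and signs disappeared or basically disappeared, and syndrome scores were reduced by ≥95"%. Below it come a grade at 70%, a grade at 30% or more (run into the same item, with no label of its own) and an ineffective grade below 30%.

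Section 2.7 (Statistical analysis) attaches tests to types of data:

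- Measurement data: t test if normal, rank sum test if not.
- Count data: "count data are expressed by rate and composition ratio, and comparison is performed by chi-square test".
- Repeated measurements: repeated-measures analysis of variance and MANOVA.
- A marginal homogeneity test is also named, in a sentence fragment attached to no data type.

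No sentence says which test the grades receive.

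The design behind the comparison is also described in two ways. Section 2.3 makes participants their own controls, with untreated scars as the blank control. Section 2.6 has envelopes opened to determine grouping, and section 2.5 counts patients per group: "a minimum of 49 patients per group is needed".

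**The concern.** The grades are categories that would be reported as counts and proportions, so the count-data rule is the one that naturally covers them. Pearson chi-square treats the four grades as unlabelled boxes. Its P value does not change if the grades are permuted, and it spends 3 degrees of freedom on a question with one direction: do treated scars reach better grades? Two things follow.

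- A real, consistent shift towards better grades is more likely to be reported as non-significant than with a test that uses the order.
- A significant result says only that the grade patterns differ. The direction has to be read off the table.

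If treated and untreated scars belong to the same patients, the independence that chi-square assumes also fails. That is a more basic fault than the lost order.

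**Working it through.** **Inputs from the article.** Section 2.5: a difference of 11 points ("expected mean difference between groups of 11 points of the Constant–Murley questionnaire"), "with a value of a = 0.05 (probability of committing a type I error) and a statistical power of 95"%, 49 per group, then "increased by 20% after considering the potential dropouts, finally including 60 patients for each group". Section 2.4.2: cut-offs at 95%, 70% and 30%. The article gives no standard deviation, sidedness or expected grade rates.

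**The plan's own figure.** With n = 2(1.960 + 1.645)² SD² / 11² per group (two-sided alpha assumed), SD 14 gives 42.1, so 43. SD 15 gives 48.3, so 49. SD 16 gives 55.0, so 55. The stated 49 therefore implies an SD near 15, but cannot be reproduced without assuming one. For dropout, 49 × 1.2 = 58.8 and 49 / 0.8 = 61.25; the stated 60 lies between them. These figures concern the Constant–Murley questionnaire. The article states no power for the grades, so everything below rests on assumptions.

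**Check 1: cost of the degrees of freedom.** Take the noncentrality that gives a 1-df test a stated power at alpha 0.05, and apply it to a 3-df test.

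| Power, 1 df | Power, 3 df | Loss (points) |
|---|---|---|
| 50% | 35% | 16 |
| 80% | 65% | 16 |
| 90% | 78% | 12 |
| 95% | 87% | 8 |

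**Check 2: simulated grade tables, 60 independent patients per group.** Assumed control distribution: 50% ineffective, then 30%, 15% and 5% in rising grades. The treated group is shifted by a common odds ratio (OR). Pearson chi-square on the 2×4 table is compared with the tie-corrected rank sum test.

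| OR | Chi-square | Rank sum | Gain (points) |
|---|---|---|---|
| 1.5 | 14% | 22% | 8 |
| 2 | 37% | 53% | 16.5 |
| 2.5 | 61% | 78% | 17 |
| 3 | 78% | 90% | 12 |
| 4 | 94% | 98% | 4 |
| 6 | 99.7% | 100% | 0.3 |

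Over the assumed control distributions (25% to 97% ineffective), the gain at 60 per group is about 4 to 19 points wherever the rank test's own power lies between about 10% and 98%.

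**Check 3: grading a continuous fall, 49 per group.** Normal percentage falls, control mean 10% to 50%, SD 20 or 30 points, cut at 30, 70 and 95. The t-test power equation with 49 per group gives an effect of 0.736 SD for 95% power and 0.572 SD for 80%.

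| Effect | Chi-square on grades | Rank sum on grades | t test on ungraded fall | Gain, rank sum over chi-square (points) |
|---|---|---|---|---|
| 0.736 SD | 70–80% | 77–92% | about 95% | 6–14 |
| 0.572 SD | 45–56% | 53–74% | 77–81% | 5–20 |

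**Where the range breaks.**

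- OR 6 or more with 70% or fewer controls ineffective, 60 per group: the gain is under 1 point, because both tests are near 100%.
- Controls all ineffective against 90/8/2/0%: the gain is 19 points at 60 per group and 24 at 49.
- Shift confined to the upper grades (40/40/15/5% against 40/20/30/10%, 60 per group): chi-square has 67% and the rank test 23%, a reversal of 44 points.

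None of these figures carries over to a within-patient comparison, because all assume independent groups.

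**The case against.** The strongest reply is that the plan never sends the grades to chi-square. Section 2.7 also names a marginal homogeneity test. That test is for paired categories, so it does not fit the measurement data it follows, and under section 2.3 paired grades would be its natural use. A rate could also mean a two-category effective rate cut at 30%, where order across grades no longer matters to the test. This stands in part. The wording is unclear and is not a firm choice of an order-blind test. But chi-square is the only test tied to count data, and the fragment is tied to nothing, so the text needs settling on either reading.

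A reader might infer that the trial will lose 5 to 20 points of power. The article does not support that. It gives no grade rates. The 0.74 SD benchmark is back-solved from a sample size built on a questionnaire that is not among the outcomes in section 2.4, and the 80%-power case is not the plan's. The size, and even the sign, of the difference depend on how the shift falls across the grades.

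A reader might also infer that the main conclusion is at risk. Section 2.4.1 makes the Vancouver total score the main efficacy standard, and the grades only cut up the fall in that score. The scores have tests of their own in 2.7. The point about direction is modest too, since the composition table would show which condition did better.

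**Conclusion.** The point holds in a conditional form. The grades are ordered by construction. The one rule in 2.7 that fits them ignores order and, under self-control, pairing as well. Two independent sets of assumptions agree on size: if chi-square is applied to four grades in two independent groups of 49 to 60, and the effect is a moderate shift running consistently through the grades, it gives up roughly 5 to 20 points of power to a rank sum test. The loss is near zero for large effects, and chi-square can win when the shift touches only some grades. If the comparison is within patient, the objection to chi-square is stronger, because independence fails, but the figures above do not measure it. The change is worth making because it is a better method at almost no cost. The main efficacy result does not depend on it.

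**What to change.** Add to section 2.7 that the efficacy grades of section 2.4.2 are compared by a test that uses their order, with one value per patient and condition:

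- If the comparison is between patients: Wilcoxon rank sum or linear-by-linear trend test.
- If it is within patient: signed-rank or ordinal marginal homogeneity test, which would also give the stray mention in 2.7 a stated purpose.

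Keep chi-square for unordered, independent counts. State that the graded result supports the comparison of the ungraded total score.

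The cost is a sentence or two of text, with no extra patients, visits or data. Section 2.9 says recruitment has not started, so the choice can be fixed before any result is seen. The one downside is less sensitivity to differences that do not run in one direction through the grades; the composition table would still show these.
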